### Sample size and power considerations

The sample size is calculated to test the superiority of the PR protocol over the UC protocol in the assessment of change in the WORC physical symptoms subscale at week 12 (primary outcome) [75]. With 41 patients per group, the study will have 80% power assuming the expected group difference in the mean changes from baseline is 12 points, corresponding to the suggested minimum clinical relevant difference [47], the common standard deviation is 20 (0–100 scale) [75] and a significance level of 5%. With an expected dropout around 20% during the study we will randomize and allocate 100 patients (50 to each group); analyzing the intention to treat (ITT) population, which will give power of 85% to detect the aforementioned difference. A provisional deadline for patient recruitment is set to June 2018, but in case the target number of 100 patients has not been met the recruitment period may be extended to reach the number required (2 times 41 patients) to obtain power of at least 0.8 (80%).

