**Methods:**

The current study is a randomized, controlled, outcome-assessor blinded, multicenter, superiority trial with a two-group paralleled design. A total of 100 patients with surgically repaired traumatic rotator cuff tears will be recruited from up to three orthopedic departments in Denmark, and randomized to either a progressive early passive and active movement program or a limited early passive movement program (usual care). The primary outcome measure will be the change from pre-surgery to 12 weeks post-surgery in the Western Ontario Rotator Cuff Index questionnaire. Secondary outcomes include the Disabilities Arm, Shoulder and Hand questionnaire (DASH), range of motion, strength and tendon healing characteristics from ultrasound measurements at 12 months follow up.

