**Fig. 2 Fig2:**
[figure not shown]
Time schedule of enrollment, assessments and responsible trial personnel (Standard Protocol Items: Recommendation for Interventional Trials (SPIRIT)). [name], primary investigator; SW, co-author; N/A, not applicable; OA: outcome assessors; MD, medical doctor/ radiologist; WORC, Western Ontario Rotator Cuff Index; DASH, Disabilities Arm, Shoulder and Hand questionnaire; MRI, magnetic resonance imaging; GRS, Global Rating Scale; NPRS, numeric pain rating scale; ROM, range of motion; US, ultrasound

The primary outcome is the 12-week change in the WORC [47]. The WORC is a self-administered questionnaire developed (by interviewing patients) to measure health related quality of life (HRQL) in patients with rotator cuff disorders and it consists of 21 items in 5 domains: physical symptoms (6 items), sports and recreation (4 items), work (4 items), lifestyle (4 items) and emotions (3 items). Each question is scored on a 100 mm visual analogue scale (VAS) and summed to a total score for each domain, with a higher score indicating reduced quality of life. By inverting the raw score and then converting it to a percentage score ((2100–1875)/2100 × 100 = 10.7%)) each domain ranges from 0 (worst possible) to 100 (best possible) [47, 48]. The WORC has excellent reliability with intra class correlation (ICC) between 0.84 and 0.99 [49, 50] and a minimal clinical important difference (MCID) of approximately 12% [47, 49, 51]. A recent translated and cross-culturally adapted Danish version was found valid in patients with rotator cuff tear (high correlation with the DASH (0.71), and test re-test reliable (ICC of 0.80 95% CI 0.69–0.87)) [52].

Secondary patient-reported outcomes (PRO) include assessment of pain, functional activity level and HRQOL, using the DASH [53]. The DASH questionnaire is a self-administered questionnaire and is region-specific to upper extremity disorders and consists of 30 items divided into 6 items on symptoms and 24 on function. The questionnaire score ranges from 0 to 100 where 0 equals no disability and 100 equals the most severe disability [53]. The DASH is generated by asking questions of patients with upper extremity problems/disability and is valid, reliable and responsivene for this patient group [53, 54]. The Danish validated version was to found to be a reliable [55] and responsive outcome measure in a variety of Danish-speaking patients with orthopedic upper extremity problems [56].

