### Statistical analysis plan

The primary efficacy analysis performed is assessment of the between-group difference in change in the WORC score after 12 weeks in the ITT population. The ITT population is defined as all randomized patients irrespective of compliance or withdrawals. Missing data will be replaced using a multiple imputation technique with age, gender, center, group allocation (masked) and baseline values as predictors. For sensitivity purposes missing data will be imputed using baseline observation carried forward (BOCF). The modified ITT population is defined as the ITT population that has a valid baseline observation of the variable of interest. The as-observed (AO) population is defined as patients who have the outcome of interest assessed at a given time point of interest (i.e. no imputation of missing data will be done).

The per-protocol (PP) population is defined as patients in the AO population that adhere to this protocol, defined by the criteria of the two groups: the PR group (Table 1), included in the AO population and have attended at least 75% of the scheduled rehabilitation appointments, whether at clinical visits or home-based as tailored to the individual (documented by the exercise logbook), and do not stop the intervention during the 12-week main trial period and do not engage in concomitant exercise therapy (e.g. private physiotherapy sessions, acupuncture); and the UC group (Table 1), included in the AO population, and do not stop the intervention during the 12-week main trial period and do not engage in concomitant exercise therapy. Each patient registers the home shoulder exercises in an exercise logbook, and successful completion of the intervention is defined as performance of 75% of the planned exercises.

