The primary analysis at week 12 will be by analysis of covariance (ANCOVA) on change from baseline in the WORC domains as dependent variables, with group allocation (two levels) and time (week 6 and 12), gender and site as fixed factors, whereas age and baseline values will be analyzed as covariates. Secondary outcome measures will be analyzed by multiple logistic regression for binary outcome measures (re-tear, tendon healing, recurrence of symptoms (e.g. pain and function), complications) and by ANCOVA for the continuous outcome measures (pain, patient-reported outcomes, surgery information, strength, ROM) as dependent variables (individually), with group allocation and time as fixed factors, and site and baseline values as covariates. Predictors of health outcomes will be analyzed by ANCOVA or multiple regression as independent variables, with change in the WORC as the dependant variable. All statistical tests will be two-sided and statistical significance will be denoted by a computed *p* value equal to or less than 0.05. All data analysis will be carried out according to a pre-established analysis plan. The statistical analysis plan (SAP) will be carried through blinded according to group allocation, and results will be interpreted in an author consensus statement prior to disclosing/revealing group allocation on the basis of a blinded review of the data from the primary endpoint (changes from treatment A compared to changes from treatment B), assuming that treatment A is the active treatment (PR), and the other assuming that treatment B is the active treatment (UC). Analysis of the primary outcome will be calculated blinded, and two interpretations will be performed based on whether PR or UC is superior. Not until signed consent from all of the authors of this trial (identical to the authors of this SAP) has been obtained, agreeing on one interpretation of the results only, will the randomization code be broken. This is to reduce bias in the interpretation of the current findings. On agreement, all members of the author group will approve and sign the interpretations before any publication procedures are initiated [76].

The protocol conforms to the recommendations of the Enhancing the Quality and Transparency Of health Research (EQUATOR) network [77] using the Standard Protocol Items: Recommendations for Interventional Trials (SPIRIT) checklist and the Consolidating Standards of Reporting Trials (CONSORT) statement [78] (Additional file 3).

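### The protocol names the primary outcome inconsistently: the WORC as such, its physical symptoms subscale, or all five WORC domains, with no deciding score identified

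*Protocol article*

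**What the plan says.** The article describes the primary outcome in five places.

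- **Abstract, Methods:** "change from pre-surgery to 12 weeks post-surgery in the Western Ontario Rotator Cuff Index questionnaire".
- **Outcome measures/variables:** "The primary outcome is the 12-week change in the WORC".
- **Statistical analysis plan, opening:** "assessment of the between-group difference in change in the WORC score after 12 weeks in the ITT population".
- **Sample size and power considerations:** "assessment of change in the WORC physical symptoms subscale at week 12 (primary outcome"). The calculation uses a 12-point difference, SD 20 on a 0–100 scale and 5% significance. It claims 80% power with 41 per group and 85% with 50 per group.
- **Statistical analysis plan, primary model:** "analysis of covariance (ANCOVA) on change from baseline in the WORC domains as dependent variables".

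The outcome section says of the WORC that "it consists of 21 items in 5 domains: physical symptoms (6 items"), followed by sports and recreation (4), work (4), lifestyle (4) and emotions (3). It says that "each domain ranges from 0 (worst possible) to 100 (best possible"), and illustrates the conversion with (2100 − 1875)/2100 × 100 = 10.7%. It gives a minimal clinically important difference of about 12% for the WORC. The analysis section makes all tests two-sided and calls p ≤ 0.05 significant.

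**The concern.** A superiority trial needs one variable, known in advance, whose test decides the claim. Here three candidates carry the word primary: the WORC without qualification, one of its five subscales, and the set of domains. Each can be defended from the text, and each could be reported as the pre-specified result if it turned out significant.

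The planned blinded interpretation does not close this gap. It has the authors agree on what the result means before they know which arm is which. It does not settle which WORC score that result is.

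The power statement has the same weakness. It is tied to physical symptoms, so if another score is the primary one, the article gives no variance for it.

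**Working it through.** **1. The definitions side by side**

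| Place | Primary variable |
|---|---|
| Abstract; outcome section; opening of analysis section | the WORC / the WORC score, no subscale named |
| Sample size section | physical symptoms (6 of 21 items) |
| Primary ANCOVA | WORC domains, plural (five are listed) |

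None of these entries uses the word total for the primary outcome. The whole-instrument reading is natural, given the unqualified name and the 2100-point example, but it is an inference.

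**2. The plan's own sample size figures**

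Inputs from the sample size section: δ = 12, σ = 20, two-sided α = 0.05, 1:1 allocation.

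- n per group for 80% power = 2(1.960 + 0.842)² × 20²/12² = 43.6, so 44 (45 with the t distribution).
- Power at 41 per group: 12/(20√(2/41)) = 2.717, and Φ(2.717 − 1.960) = 77.5% (76.5% with t). The stated 80% is not reproduced.
- Power at 50 per group: 12/(20√(2/50)) = 3.0, and Φ(3.0 − 1.960) = 85.1% (84.4% with t). The stated 85% is reproduced, provided all 100 patients contribute full information.

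The shortfall at 41 is a separate matter, but it should be put right when the power is restated.

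**3. False-positive risk if several scores count as primary**

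Five independent tests at 0.05: 1 − 0.95⁵ = 22.6%. Domains of one questionnaire are correlated, and the article gives no correlations, so a range is assumed. The table is a simulation of 500,000 draws of five equicorrelated z-statistics. The whole-instrument score is the item-weighted sum (6, 4, 4, 4, 3 over 21). Simulation error is about 0.05 percentage points.

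| Assumed correlation | Five domains | Five domains + whole score | Physical symptoms + whole score only |
|---|---|---|---|
| 0 | 22.64% | 24.33% | 8.67% |
| 0.5 | 18.25% | 18.42% | 7.62% |
| 0.7 | 14.83% | 14.86% | 7.03% |
| 0.8 | 12.68% | 12.69% | 6.63% |
| 0.9 | 10.18% | 10.18% | 6.19% |

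**4. Power if the whole-instrument score is primary**

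The article gives no SD for this score. With an assumed SD of 15 to 25, δ = 12 and 41 per group:

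- SD 15: 12/(15√(2/41)) = 3.622, power 95%.
- SD 25: 12/(25√(2/41)) = 2.173, power 58%.

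**5. The scoring example**

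With 100 mm per item, the domain maxima are 600, 400, 400, 400 and 300, which sum to 2100. Dividing by 2100 therefore scales the 21-item total. Applied to physical symptoms, the worst possible score would be (2100 − 600)/2100 = 71.4, which contradicts the stated domain range of 0 to 100.

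**The case against.** The strongest reply is that the sample size section is the only place that attaches the label to one specific score. On that view the Abstract and the outcome section merely name the instrument, and the sample size section says which score of it is meant. A reader might infer that the trial is powered on a different endpoint from the one it declares. The article does not establish that, because on this reading the two agree. What remains even then is that the primary model uses the domains in the plural, so the conflict does not disappear.

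A second reply is that a multiplicity rule may stand in the separate analysis plan to which the article refers. That is fair, and the absence of a rule here is not the point. The point is that this document does fix the primary variable and does so in conflicting ways.

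Other strong readings are also unsupported:

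- **Six separate chances of success.** Five domains plus a total is the upper count, but the total is a weighted sum of the domains. From a correlation of 0.5 upward it adds at most about 0.2 percentage points.
- **The 12-point difference is wrong for a subscale.** The article gives about 12% for the WORC and relies on one of the same cited sources for the 12 points. Which score that source reports cannot be checked here.
- **The domains will be mis-scored.** The stated 0–100 domain range, repeated in the sample size section, excludes dividing a domain by 2100. This is a whole-instrument example attached to the wrong word, not an operative scoring rule.

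**Conclusion.** The point holds as an inconsistency in what decides the trial. Three places give the WORC without qualification, one gives physical symptoms, and one gives the domains.

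The consequence depends on which reading is acted on. Testing all five domains as primary at 0.05 gives a family-wise error of 22.6% if they are independent and about 18%, 15%, 13% and 10% at correlations of 0.5, 0.7, 0.8 and 0.9. A choice between the whole-instrument score and physical symptoms alone gives about 6% to 9%. The correlations are assumptions. The error rates also assume that any significant candidate would be claimed as primary, which the text permits but does not state as an intention.

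The power for a whole-instrument primary outcome cannot be derived from the article. The range of 95% to 58% at 41 per group rests on an assumed SD of 15 to 25.

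**What to change.** Before the data are analysed:

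1. Name one WORC score at week 12 as the single primary variable. Use it in the same words in the Abstract, the outcome section, the sample size section, and both the opening and the primary model of the analysis section.
2. Make all other WORC scores secondary. The whole-instrument score is the natural choice from the Abstract, the outcome section and the opening of the analysis section. Physical symptoms is the score on which the sample size was built. Either is workable if used consistently.
3. Tie the 12-point difference and the SD to the chosen score. For the whole-instrument score, supply a sourced SD and restate the power.
4. Correct the scoring text. Keep the 2100 example for the 21-item total, and scale each domain by its own maximum (600, 400, 400, 400, 300).

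**Cost:** no new data collection, because all items of the WORC are already gathered. It is not only a change of wording, however: the stated power may change, and no primary claim can then rest on any other WORC score.

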**Fig. 1 Fig1:**
[figure not shown]
Expected flow of patients through the study. PR, progressive rehabilitation; UC, usual care

The second phase includes the secondary endpoint 52 weeks after baseline, at which point Ultrasound (US) measurements are included in the outcome assessments. During the 40-week follow up period (from week 12 to week 52) most patients continue standard rehabilitation in the community for 4–8 weeks. The community care providers are not informed about initial treatment to which each patient has been allocated (unless the patients tell them) and can thus be considered quasi-blinded.

After 12 weeks no study-related activities are performed, except for the 12-month follow up and treatment of any adverse events that might occur during the trial (52 weeks). Patients are randomized equally (1:1) to receive either PR or UC (Fig. 1).

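### On the stated inputs 41 patients per group gives about 77% unadjusted power, not 80%, so the fallback of 2 × 41 misses its own 80% floor even with complete data

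*Protocol article*

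**What the plan says.** All of the design figures stand in the protocol article under Sample size and power considerations.

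- The main statement: "With 41 patients per group, the study will have 80% power".
- Its inputs: "the expected group difference in the mean changes from baseline is 12 points" and "the common standard deviation is 20 (0–100 scale"), at a 5% significance level.
- The planned size: "With an expected dropout around 20% during the study we will randomize and allocate 100 patients (50 to each group"). Power for these 100 in the intention-to-treat population is put at 85%.
- The fallback: if 100 has not been met by the provisional deadline of June 2018, the recruitment period may be extended to "reach the number required (2 times 41 patients) to obtain power of at least 0.8 (80"%).

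Two further inputs stand elsewhere. Under Statistical analysis plan: "All statistical tests will be two-sided". Under Methods/design: "Patients are randomized equally (1:1) to receive either PR or UC".

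**The concern.** The section gives every input of a standard two-group comparison of means, so its power figures can be checked directly. The figure for 41 per group fails that check, while the figure for 50 per group passes on the same inputs. The two statements therefore cannot come from one calculation.

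The wrong figure also serves as a recruitment threshold. The article says that 82 patients secure power of at least 80%, and a steering committee that relied on this could accept 82 in the belief that the design requirement was met. The same paragraph expects about 20% dropout, yet the fallback carries no explicit allowance for it.

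**Working it through.** **Inputs.** Difference 12, common SD 20, 5% level (Sample size and power considerations); two-sided tests (Statistical analysis plan); 1:1 allocation (Methods/design). The standardised difference is 12/20 = 0.60.

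**Formula.** With n per group, the normal approximation is power = Φ(0.60 × √(n/2) − 1.960). The exact version uses the noncentral t distribution with 2n − 2 degrees of freedom.

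**Step 1: the 85% at 50 per group.** 0.60 × √25 = 3.000, and Φ(3.000 − 1.960) = Φ(1.040) = 85.1%. The t-test gives 84.4%. The stated 85% reproduces, two-sided and without covariate adjustment, which confirms this reading of the inputs.

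**Step 2: the 80% at 41 per group.** 0.60 × √20.5 = 2.717, and Φ(2.717 − 1.960) = Φ(0.757) = 77.5%. The t-test gives 76.5%. A one-sided test does not explain the figure either: it gives 85.8% (normal) or 85.3% (t) at 41 per group.

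**Step 3: the number needed for 80%.** n = 2 × (1.960 + 0.842)² × (20/12)² = 43.6, so 44 per group by the normal approximation (80.4%). By the t-test 44 gives 79.5% and 45 gives 80.4%, so 45 per group, or 90 in total.

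**Step 4: what would make 41 sufficient.** With the t-test, 41 per group reaches 80% if the SD is about 19.2 instead of 20, or if the true difference is about 12.5 instead of 12. The section states neither.

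**Step 5: loss to follow-up.** The 20% is given for the whole study, which runs 52 weeks; the primary endpoint is at week 12. Loss by week 12 is not stated, so a range is shown.

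| Starting number per group | Loss by week 12 | Observed per group | Power, t | Power, normal |
|---|---|---|---|---|
| 41 | none | 41 | 76.5% | 77.5% |
| 41 | 10% (assumption) | about 37 | 72.1% | 73.3% |
| 41 | 20% (worst case) | about 33 | 67.0% | 68.3% |
| 50 | none | 50 | 84.4% | 85.1% |
| 50 | 20% (worst case) | 40 | 75.5% | 76.5% |

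The rows with loss apply only if the starting number counts randomised patients.

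**The case against.** **The planned analysis may recover the shortfall.** The primary analysis is an ANCOVA with baseline value, age, gender and site. If 20 is the unadjusted SD, a residual SD of 19.2 would bring 41 per group to 80%. That requires the covariates to explain about 1 − (19.2/20)² ≈ 8% of the variance, which is modest. This stands as a reason to label the corrected figure as unadjusted. It does not rescue the text, because the section claims no such gain and its 85% uses none. With a residual SD of 19.2, 50 per group would have about 87–88% power, so the two stated figures would still disagree.

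**The intention-to-treat analysis with multiple imputation keeps every randomised patient.** True, but imputation does not in general restore the information lost with a missing week-12 outcome. Even with full information from all 82, power is about 77%.

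**The shortfall is small.** With complete data it is, at 3 to 4 patients per group. This stands and limits the weight of the point.

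**Two stronger readings are not supported.**

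- A reader might take 2 × 41 as a cap on recruitment. The article presents it as a number to reach if the deadline passes, and Trial status says that recruitment continues until the complete sample size is achieved.
- A reader might take 67% as the power of the fallback. That needs two assumptions that the article does not state: that the 82 are randomised patients, which is likely since the sentence concerns recruitment, and that the full 20% dropout has occurred by week 12.

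**Conclusion.** The statement that 41 per group gives 80% power is wrong on the article's own inputs. The correct unadjusted figure is 76.5% (t) or 77.5% (normal), and 80% needs 45 or 44 analysed per group. The fallback therefore misses its promised floor by 2.5 to 3.5 points with complete data, and by more if the 82 are patients randomised rather than patients observed at week 12.

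The 85% for 50 per group is correct arithmetic, but it holds only if all 100 patients contribute full week-12 information. A reader might infer that the planned 100 is therefore safe whatever the dropout. It is not: by the same reasoning, a 20% loss by week 12 would leave the main target at about 76%. Nor do the documents establish that 100 is too few, since loss by week 12 and any covariate gain are both unstated.

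The conclusion assumes a two-sided, unadjusted comparison of mean changes. That the 85% reproduces on exactly those terms supports the assumption.

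**What to change.** In Sample size and power considerations:

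1. State that 41 per group gives about 77% unadjusted power, and that 80% needs 45 analysed per group (90 in total).
2. Express the fallback as a number of patients with a week-12 WORC, or keep 82 and state its true power in place of the promise of at least 80%.
3. State that the 85% at 100 patients assumes no loss of information, and that 40 per group after a 20% loss would give 75.5–76.5%.
4. If the authors rely on a gain from the ANCOVA, state the assumed residual SD or proportion of variance explained, and apply it to both power figures.

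The cost is corrected text and slightly less favourable stated power. No change in enrolment is requested.
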